### Data management

The data will be collected by two independent authors and stored in an SPSS® file database. The tools used to obtain the outcomes will be evaluated at the beginning (week 0) and after the intervention (week 8) and again at three and six months *follow-up*. All forms will be made available via *Google Forms.*

One of the researchers will send a WhatsApp message every week to promote participant retention and complete follow-up, encouraging participants to come to the meetings. Also, the messages sent will be the same for both groups and will include reminders about the meeting days, location, time, and any materials participants may need to bring for the activities. To those who discontinue or deviate from the intervention protocol, all data exclusion will be necessary.

The data collected will be saved on an institutional drive linked to the researcher in charge and shared only with the other researchers in the study. The data are expected to be stored for two and a half years (until the end of 2025), following the study schedule.

An interim analysis could be conducted if preliminary results need to be presented at scientific events relevant to the institutions involved in the study’s development. However, if such analyses could compromise the reliability of the data, they will not be performed*.* All authors could have access to interim results, but only the study coordinator ([name]) could decide to terminate the trial.

The plans for investigators and sponsor to communicate trial results are: a) Individual disclosure of the basal and post-intervention results to each participant; b) A public seminar with grouped results at sponsor institution to healthcare professionals; c) Public disclosure in scientific events, preprint, and scientific article publication.

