### Recruitment

Recruitment will take place from March 4, 2024, to March 31, 2026, which is the estimated timeframe to achieve the calculated sample size. Participants will be recruited through posts on the researchers’ social networks, and those who express an interest will be contacted for an initial conversation via WhatsApp video call. This assessment will confirm the participant’s desire to participate in the study, the inclusion and exclusion criteria, and guidance on the study protocol. After confirming eligibility and signing the Informed Consent Form, the participants will be randomized and assigned to one of the two intervention groups: self-compassion or diet. The groups will take place weekly through face-to-face meetings, which will take place over eight weeks and will be one hour long. The group will be led by nutritionists previously trained in the two approaches. The adherence rate will be controlled, requiring a minimum participation of 75% (6 meetings) to be maintained in the entire study (baseline to eight weeks, three and six months follow-up).

Before the first meeting, all participants will answer an anamnesis and three validated scales for assessing eating behavior and body dissatisfaction, which will be available through the *Google Forms* platform. The same scales will be answered after the eight meetings (the end of the group), three months after the last meeting, and six months after the last meeting. Fig 2 shows the study flow diagram.

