### Adherence, modifications, and concomitant care

In both groups, the importance of attendance and commitment to the meetings will be discussed. It will also be emphasized that it will be a safe space for listening, welcoming, and confidentiality. Participants will be asked about their feelings and doubts about their study process. The meetings will always occur on the same predetermined day, time, and location. Participants will be notified via smartphone before each meeting as a reminder. To increase adherence and commitment to the study, participants will also be offered activities to practice at home, such as food records, observation, and reflection exercises, or they will be asked to bring materials related to the next meeting (e.g., food packaging).

Adherence to the proposed interventions will be checked at each meeting. However, the difficulty of carrying out what is proposed does not compromise remaining in the group meetings.

Participants cannot change the group they have been allocated to. However, they are free to leave the study as they wish. The meeting protocol for both groups cannot be modified, as this could bias the study.

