### Sample size

Considering the study by Albertson, Neff and Dill-Shackleford (2014) [40], which found an improvement in body dissatisfaction from meditation based on self-compassion techniques with an effect size of 0.73 (high), a sample size of 76 people (38 for each group) was calculated. This calculation considered a power of 80%, a significance level of 5% and a Cohen’s d of 0.7 to test whether there is a minimal difference in the body dissatisfaction averages and self-compassion levels between the intervention and control groups, already including an addition of 10% for possible losses and refusals.

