### Randomization, allocation and masking of groups

Participants will be randomized to the Self-Compassion or Diet group with 1:1 allocation in the Random Group Generator (https://pt.rakko.tools/tools/59/). The nutritionists responsible for applying the interventions will have no contact with the randomization and will not know in advance who will go to which group, only the research coordinator.

Due to the nature of the intervention, it is not possible to blind the researchers and participants during the study’s conduction after the randomization process. However, the intervention and control groups will not interact in any way. Likewise, the statistical analysis will be blinded to the evaluator.

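### Data from randomised women who discontinue or deviate are to be excluded, so the only comparison described is among completers and is open to selection bias of unknown size and direction

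*Protocol article*

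**What the plan says.** Four places in the protocol article bear on who is analysed.

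- **Data management:** "To those who discontinue or deviate from the intervention protocol, all data exclusion will be necessary". The sentence is not limited to data collected after the event, and it does not define a deviation.
- **Recruitment:** "The adherence rate will be controlled, requiring a minimum participation of 75% (6 meetings) to be maintained in the entire study". A bracket after these words spells out the span: baseline to week 8, then the 3- and 6-month follow-ups. The sentence does not mention deleting data.
- **Adherence, modifications, and concomitant care:** women cannot change group. "However, they are free to leave the study as they wish". The section also says that "the difficulty of carrying out what is proposed does not compromise remaining in the group meetings".
- **Statistical analysis:** a repeated-measures general linear model with a group-by-time interaction, run separately from baseline to each follow-up. No analysis population is named.

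Allocation is 1:1. Under Randomization, allocation and masking of groups, the protocol says that participants and researchers cannot be blinded once women are randomised, and that the statistical analysis will be blinded.

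**The concern.** Randomisation makes the two groups comparable at the moment of allocation. Discontinuing, deviating and attending fewer than 6 meetings all happen later. The programmes differ greatly: one prescribes a calculated food plan, the other consists of reflection and mindfulness exercises. Women know which one they have. The reasons for leaving, and the kind of woman who leaves, can therefore differ between the arms.

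The protocol's own Introduction and Discussion link restrictive dieting with guilt, a sense of failure and dysfunctional eating. A woman who reacts to the diet in that way is a plausible candidate to stop or deviate. Her body dissatisfaction and eating behaviour scores are exactly what the trial sets out to measure, and the rule would remove them. Selective loss from the self-compassion arm would act in the opposite direction.

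Two features make this harder to repair later. First, because the rule covers all data and low attenders are not kept for follow-up, a later analysis plan would have little from which to restore an as-randomised comparison. It might not even be possible to describe who was lost. Second, with deviation undefined and staff unblinded, exclusions could be judged case by case by people who know the allocation.

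**Working it through.** **1. The plan's sample size.** Inputs from the Sample size section: Cohen's d = 0.7, power 80%, significance level 5% (taken as two-sided), 1:1 allocation, 10% for losses. A two-sample t-test needs 33.02 per group, rounded up to 34. Then 34 / 0.9 = 37.8, rounded up to 38 per group, and 2 × 38 = 76. The stated figure reproduces, so there is no error in N.

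**2. Which women the text removes.**

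| Event after randomisation | Text | Consequence |
|---|---|---|
| Discontinues | Data management | All data excluded (stated) |
| Deviates from the intervention protocol | Data management | All data excluded (stated; deviation undefined) |
| Attends fewer than 6 meetings | Recruitment | Not maintained in the study (stated); data lost (inferred by reading it with Data management) |
| Attends, but has difficulty with the proposed tasks | Adherence | Stays in the meetings (stated); data kept only if this is not a deviation (unclear) |

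What remains for the general linear model is the set of women who completed as prescribed.

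**3. Size of the bias, illustration only.** The documents give neither exclusion rates nor their relation to outcome, so both are assumed. Let the outcome be standard normal in both arms with no true effect and higher values worse. Let a propensity to be excluded have correlation ρ with it, and let the fraction e with the highest propensity be excluded. The mean of those retained is then

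−ρ × φ(z) / (1 − e), where z is the (1 − e) quantile of the standard normal and φ its density.

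- e = 10%: φ(z) / (1 − e) = 0.1755 / 0.9 = 0.195
- e = 30%: 0.3477 / 0.7 = 0.497
- e = 40%: 0.3863 / 0.6 = 0.644

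Spurious difference between arms:

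- 10% versus 30%: ρ × (0.497 − 0.195) = ρ × 0.302, which is 0.09 SD at ρ = 0.3 and 0.15 SD at ρ = 0.5
- 10% versus 40%: ρ × (0.644 − 0.195) = ρ × 0.449, which is 0.13 SD at ρ = 0.3 and 0.22 SD at ρ = 0.5

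A simulation with 38 women per arm, 20,000 replicates per scenario and a t-test on those retained agrees with these differences and gives the type I error:

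| Excluded, arm 1 / arm 2 | ρ = 0 | ρ = 0.3 | ρ = 0.5 |
|---|---|---|---|
| 10% / 10% | 4.9% | 5.3% | 4.8% |
| 10% / 30% | 4.9% | 6.5% | 9.4% |
| 10% / 40% | 5.1% | 7.7% | 13.4% |

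Bias is about zero when exclusion is unrelated to outcome (ρ = 0). It is also about zero when the rates are equal, given the same ρ in both arms as simulated here. In this model the arm that loses more women is flattered.

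**4. What analysing all women does to power.** With 38 per group and complete data, power at d = 0.7 is 85.3%. That figure assumes the effect stays at 0.7 when non-attenders are included. If non-attenders gain nothing relative to the other arm, the average effect shrinks:

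| Non-attendance per arm | Diluted d | Power, all 38 analysed | Power, completers only at d = 0.7 |
|---|---|---|---|
| 10% | 0.7 × 0.9 = 0.63 | 77% | 81% |
| 20% | 0.7 × 0.8 = 0.56 | 67% | 77% |
| 30% | 0.7 × 0.7 = 0.49 | 56% | 71% |

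If non-attenders keep half the effect, 30% non-attendance gives d = 0.7 × 0.85 = 0.595 and power 73%, close to the 71% for completers.

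**The case against.** The strongest reply is that selective exclusion is only a possibility. No expected attendance or deviation rate is given, the scenarios are chosen, and balanced or outcome-unrelated exclusion produces no bias in the simulation. That stands, and it is why the figures are labelled illustrative. It does not rescue the rule, because the trial would have discarded the data needed to show that exclusion was harmless.

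Four stronger readings are tempting and are not supported:

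- **That the rule exhausts the loss allowance and breaks the 80% power.** The Sample size section describes the total as "already including an addition of 10% for possible losses and refusals". Nothing shows that exclusions would exceed 10%, and at 10% power is still about 81%. Analysing everyone may lower power through dilution. The case for change is validity, not power.
- **That the Adherence section contradicts the exclusion rule.** Its sentence concerns remaining in the meetings and follows a description of home activities. It says nothing about attendance counts or data. A woman who struggles with the tasks but attends 6 meetings satisfies both that section and Recruitment. What is left is an ambiguity over what a deviation is.
- **That the protocol expressly deletes data for attendance below 6 meetings.** This is an inference, though a natural one, from two sections read together.
- **That who stays will depend on arm and response, in a known direction.** It can. In the illustrative model, heavier loss of poor responders from the diet arm would work against the trial's own hypothesis.

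One might also say that analysis sets belong in a statistical analysis plan that is not shown. That would answer a mere silence, but here the protocol itself prescribes the exclusion.

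**Conclusion.** The concern holds in this form: the protocol prescribes exclusion of randomised women's data on grounds that arise after randomisation, leaves deviation undefined, and describes no as-randomised analysis. For every outcome and time point, the comparison described is among completers and open to selection bias.

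The size and direction of that bias cannot be determined from the documents. Under the assumed 10% versus 30% exclusion and ρ of 0.3 to 0.5, it is 0.09 / 0.7 = 13% to 0.15 / 0.7 = 21% of the planned effect. It could equally be near zero. The point should be corrected before analysis because it affects the only efficacy comparison described and because data not collected or deleted may be unrecoverable.

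**What to change.** 1. Delete the exclusion sentence in Data management, and the condition in Recruitment that ties staying in follow-up to 6 meetings.
2. State that every randomised woman is sent the week-8, 3-month and 6-month online forms whatever her attendance, unless she withdraws consent for the use of her data.
3. State that the primary analysis includes all randomised women in their allocated group, using all available data.
4. Keep attendance of at least 6 meetings as a labelled secondary per-protocol analysis, with a deviation defined in advance.
5. Reconcile Recruitment, Adherence and Data management so that remaining in the meetings, remaining in follow-up and being included in the analysis are separate statements.

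This changes data collection and analysis only, not what either group receives. N need not change on account of this point, since the stated 76 is correct for its inputs.

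The costs are an amendment communicated to the Ethics Committee, as the Ethical aspects section requires, and a little extra follow-up through forms that are already online. The effect estimate may be diluted, with somewhat lower power than among completers. Recruitment is dated from March 2024, so data from women already dropped may not be recoverable; their number by arm and the reason should then be reported.

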### Statistical analysis

Baseline characteristics of the participants will be compared between groups (self-compassion and diet). For categorical variables, the Pearson Chi-square test will be used, with continuity correction for dichotomous variables or Fisher’s exact test when at least one cell has an expected count of less than five. For continuous numerical variables, the Shapiro-Wilk test will assess normality. If normality is accepted, results will be presented as mean and standard deviation and analyzed using Student’s t-test for independent samples. If the distribution is non-parametric, data will be expressed as median and interquartile range and analyzed using the Mann-Whitney U test. No significant differences between groups at baseline are expected due to the randomization process, which should provide similar groups. However, if significant differences are observed, these variables will be included as adjustments in multivariable analyses, as described below for primary and secondary outcomes.

Comparisons between baseline and follow-up for the primary and secondary outcomes will be tested using a General Linear Model (GLM) for repeated measures, considering the interaction between group (self-compassion and diet) and time (before and after). Separate analyses will be conducted for each follow-up point: from baseline to the end of the 8-week intervention, from baseline to 3 months after the intervention, and from baseline to 6 months after the intervention. Differences will be considered statistically significant at p < 0.05. The data will be analyzed using Statistical Package for the Social Sciences (SPSS) software, version 26.0.

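### A conference-driven interim analysis open to all authors can bias this unblinded, self-report trial; the 5% error rate is at risk only if an interim result is claimed or acted on

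*Protocol article*

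**What the plan says.** The Data management section of the protocol article allows an optional look at the data: "An interim analysis could be conducted if preliminary results need to be presented at scientific events relevant to the institutions involved". It gives no number of looks, timing or endpoint. It limits the permission in one way: "if such analyses could compromise the reliability of the data, they will not be performed". It does not say how that would be judged, or by whom.

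On access and authority it says: "All authors could have access to interim results, but only the study coordinator" may decide to end the trial. It gives no grounds for such a decision.

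Four other statements bear on this:

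- Randomization, allocation and masking of groups: "it is not possible to blind the researchers and participants during the study’s conduction after the randomization process". The same section adds that "the statistical analysis will be blinded to the evaluator".
- Data management: "The data will be collected by two independent authors".
- Statistical analysis: "Differences will be considered statistically significant at p < 0.05".
- Sample size: "This calculation considered a power of 80%, a significance level of 5% and a Cohen’s d of 0.7", leading to 76 participants with 10% added for losses.

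**The concern.** The trigger for the look is a wish to present results, not safety, futility or a planned amount of information. Its stated purpose is disclosure, so between-group results could become known to the whole team, and to the public, while women are still being recruited, attending meetings and filling in questionnaires.

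This trial has little to absorb that knowledge. The outcomes are self-reported scales completed through online forms by participants who know their group. Recruitment is through the researchers' own social networks. Researchers talk with participants at every meeting to monitor adverse events (Ethical aspects). The Discussion states a hypothesis in favour of self-compassion. Emerging results could affect who volunteers, how the meetings are led and how participants answer.

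A second, conditional issue is the false-positive rate. If an interim difference could be announced as a finding, or lead to stopping, the single threshold of 0.05 would be used more than once.

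**Working it through.** **1. Is the planned sample size a single-look design?**
Inputs from Sample size: d = 0.7, alpha 0.05 (two-sided assumed, as the article does not say), power 80%, 10% for losses.
- Two-sample t-test: n = 33.02 per group, rounded up to 34.
- Loss allowance: 34 / 0.90 = 37.8, or 34 × 1.10 = 37.4. Both round up to 38.
- Total: 2 × 38 = 76, which matches the article.
- A one-sided test would give 29 per group after losses, 58 in total, which does not match.

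The figure of 76 is therefore fully explained by one two-sided test at 5%, with nothing added for an interim test.

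**2. How long could results be exposed?**
Inputs from Recruitment: enrolment from 4 March 2024 to 31 March 2026, eight weeks of meetings, last questionnaire six months after the final meeting.
- Earliest possible 8-week data: 4 March 2024 + 56 days = 29 April 2024.
- Last 6-month data, if the last woman starts on the closing date: 31 March 2026 + 56 days = 26 May 2026, then six months = late November 2026.

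Comparative data could thus exist for about two and a half years before follow-up ends, for nearly two of them with recruitment open.

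**3. What happens to the type I error?**
Let Z1 and Z2 be the interim and final test statistics for one endpoint at one time point, and t the fraction of information at the interim. Under no effect they are standard normal with correlation √t. The article gives no t, so a range is assumed.

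*Descriptive look, trial runs to its planned end, only Z2 tested:* P(|Z2| > 1.96) = 0.05 for any t. There is no inflation.

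*Either result may be claimed or acted on at p < 0.05:* error = 1 − P(|Z1| ≤ 1.96 and |Z2| ≤ 1.96).

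| Assumed t | Correlation √t | Type I error |
|---|---|---|
| 0.25 | 0.500 | 0.091 |
| 0.50 | 0.707 | 0.083 |
| 0.75 | 0.866 | 0.073 |

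**4. How reliable would an early presented result be?**
Assume half of 34, that is 17 evaluable women per group.
- Standard error of d ≈ √(2/17) = 0.343.
- Significance at 5% needs an observed d above 1.96 × 0.343 = 0.67.
- Given a significant result in the favourable direction, the mean observed d is about 0.96 if the true d is 0.7, and about 0.85 if the true d is 0.3.

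A significant difference presented at that stage would overstate the effect on average.

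**The case against.** The strongest reply is that the article promises little and forbids a good deal. The look is optional and spoken of in the singular, its only stated purpose is presentation, and it is ruled out where it might harm reliability. No efficacy stopping rule is written. The full analysis plan is not shown and could hold boundaries. The analysis evaluator is to be blinded.

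Much of this stands, and it rules out several readings that a reader might infer:

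- *That the plan inflates the false-positive rate as written.* It does so only if an interim result is claimed or acted on. A descriptive look leaves the final test at 5%.
- *That the trial may be stopped for efficacy.* The article says who may terminate, not on what grounds. Safety or feasibility would fit the text equally well.
- *That several looks are planned.* Two equally spaced interim looks plus the final test would give about 10.7%, but the article speaks of one analysis.
- *That no boundary exists.* None is stated here. That detail is commonly left to the analysis plan, so its absence is not the point.
- *That the trial has no blinding.* The evaluator's blinding is stated.

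The reply does not remove the operational problem. Blinding the evaluator does not cover the authors, who may all see the results. A stopping boundary would not undo disclosure to the team or an audience. The reliability clause, read strictly, might already forbid such a look, but with no criterion and no independent judge, the people who want the presentation also decide whether it is harmless.

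**Conclusion.** The point holds as a risk of operational bias that the article's own wording permits: a presentation-driven trigger, access for all authors, and an undefined safeguard, in a trial with unblinded researchers and participants and self-reported outcomes. The size of that bias cannot be calculated from the documents.

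The effect on type I error is conditional. It is nil for a descriptive look in a trial run to its planned end. For one look whose result may be claimed or acted on at 0.05, it rises from 5% to about 8.3%, with a range of 7.3% to 9.1%. This rests on assumed information fractions of 25% to 75%, two-sided testing, and one endpoint at one time point. Multiplicity across outcomes and follow-up times is not included.

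The article does not show that the error rate is already broken or that efficacy stopping is intended. The change is a cheap improvement, best made before any look takes place, because disclosed results cannot be withdrawn.

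**What to change.** Replace the interim-analysis paragraph in Data management with wording such as:

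> No between-group outcome comparison will be made, shared or presented before the last 6-month follow-up is complete and the database is locked. Earlier presentations are limited to the design and pooled baseline data.

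Add one sentence stating that any decision to terminate the trial will not be based on interim between-group efficacy comparisons. This clarifies a point on which the article is silent, and it leaves the weekly adverse event monitoring and any safety decision untouched.

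The single final test then keeps its 5% level, and the sample size of 76 needs no change on this account. The cost is an amendment to the text and the loss of early presentation of comparative results. The team can still present the design and pooled baseline data.
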